### Recruitment settings and procedure

Participants of the current study will be recruited at Shaanxi Provincial Cancer Hospital in Xi'an, China. We will place recruitment posters in noticeable places (e.g., waiting areas and elevators for patients) in hospital. Oncology nurses will also be involved to inform eligible patients about this study during their check-up at the outpatient clinic, and ask patients if they would be interested to participate in this study. Research assistants will contact patients whom are interested in the study to explain more about the study, and screen patients for eligibility. After confirmation of eligibility, patients who agree to participate in the study will receive an informed consent.

### Randomization

A table of randomized number will be generated by using the SAS. According to the table of randomized number, participants will be randomized to the intervention or control group with an allocation ratio of 1:1, after stratified by age, cancer stage, and breast cancer subtype. Participants will not know which group they will be allocated in.

### Intervention

The theoretical frame of the Fear-focused Self-compassion Therapy is based on the theories of FCR development as well as the theories of self-compassion related therapy such as compassion-focused therapy and mindful self-compassion therapy (31, 33, 38, 50, 51). The Fear-focused Self-compassion Therapy is an 8-week compassionate mind training intervention, and will be delivered as a group format. It is developed and tailored for Chinese young breast cancer patients by the authors including clinical psychologists, cancer nurses, and oncologists, adapted to be appropriate for Chinese young breast cancer patients and tailored to FCR. The therapy consists of eight group face-to-face sessions (60–90 min for each session) and will be delivered by three trained therapists for 8 weeks (sessions are weekly). The therapy will take place in Shaanxi Provincial Cancer Hospital, and each intervention group involves 10–15 patients. The content outline of intervention is shown in Table 1.

**Table 1 T1:** Content of fear-focused self-compassion therapy sessions.

**Session**	**Theme**	**Aims**	**Intervention content**
1.	The stability of attention	- Learn how to control the attention; - Recognize cancer-related thinking and worry; - Decrease over-identification.	- Introduce the plan, structure, confidentiality, and safety of intervention; - Introduce Fear-focused Self-compassion Therapy's theory; - Set the goals of intervention; - Introduce the attention; - Recall the experience of thinking in “automatic drive”; - Mindfulness meditation; - Discuss and set the aims, plans, and problems that may occur in home practice.
2.	Insight	- Observe your cancer-related thoughts and emotions; - Recognize your emotions and behaviors reacting to worry about cancer recurrence; - Experience the peace derived from the observation and non-involvement to the thoughts of cancer recurrence.	- Share your home practice and problems; - Deal with the problems left from last week; - Positive and negative thoughts, sensory training; - Stress response training; - Mind rest training; - Mindfulness meditation; - Image breath practice; - Discussion; - Renew the goals of home practice.
3.	The heart of self-compassion	- Understand FCR is not the direct effect of external condition, but the result of dysfunctional cognition (i.e., catastrophizing thinking, rumination, and attentional bias); - Recognize that FCR can be transformed; - Realize that you have the ability to transform and release from the fear.	- Discuss the home practice; - Introduce “Self-Compassion” and understand its components (recognize the cause of worry about cancer recurrence; realize that you have the ability to make a change; make up your mind to change); - Analyze the difference between self-compassion and self-reception; - Mindfulness meditation; - Discussion.
4.	Impartial attitude	- Decrease the absolute classification for friends, enemies, and strangers; - Understand that classification of people with their utility will hinder them from building up relationship; - Realize that everyone pursues happiness and avoids pain, and develop an impartial perspective; - Learn not to pay too much attention to cancer-related stimuli in your life.	- Discuss the home practice; - “I care/I do not care” training; - Mindfulness meditation; - Image breath practice; - Discussion.
5.	Learn appreciation and gratitude	- Recognize that your “independent” life comes from others' support; - Develop the appreciation and gratitude toward others; - Further enhance the connection with others.	- Discuss the home practice; - A network of interdependence; - Discuss “gratefulness”; - Recall the kindness from others; - Image breath practice; - Discussion.
6.	Develop empathic	- Express stronger sensibility and sympathetic for others' misfortune and happiness; - Decrease the egocentricity.	- Discuss the home practice; - Share the research of empathic; - Discuss the psychological and physiological problems about loneliness, and the desire for connection; - Discuss the empathic and accidie; - Mindfulness meditation; - Discussion.
7.	Be hopeful, love, and compassion to life	- Understand that everyone pursues happiness and avoids pain, on the basic of love and empathic; - Recognize your consistence with others; - Enhance the connection with others.	- Discuss the home practice; - Reflect on others, specifically to difficult individuals, think about how to connect with their sufferings; - Mindfulness meditation; - Image breath practice; - Discussion.
8.	Be love and compassion with commitment	- Make a commitment to future life.	- Discuss the home practice; - Review the theory of self-compassion practice; - A summary of previous practice; - Set goals for home practice at the end of the intervention.

At the first session of the therapy, participants will obtain a pamphlet about the framework and goals of Fear-focused Self-compassion Therapy, as well as activities of each session. At the end of each session of the therapy, relevant home practice will be given to participants, and at the beginning of next session, these home practice will be reviewed to discuss participants' experience during home practice. When completing the therapy, participants will receive a handbook including the content of Fear-focused Self-compassion Therapy.

To make sure that all participants receive the same treatment, new participants should not be involved in the group if the intervention starts. Also, all participants are told that if they are absent for more than one session, they have to drop out this group and can choose other groups that has not started.

### Usual care

Participants in the control group will receive usual care supported by the hospital or coming from elsewhere, and will not be offered psychological intervention for addressing FCR. Care as usual will be accessible for patients in both intervention group and the control group. Their use of usual care will be measured by Medical Consumption Questionnaire.

### Outcomes

There are five measurement time-points for all participants in the intervention group and usual care control group as above mentioned. Patients' sociodemographic and clinical characteristics (i.e., breast cancer stage, education, income, socioeconomic status, and marriage) will be assessed at baseline (T0) only. Measurement time-points of all outcomes are shown in Table 2.

**Table 2 T2:** Measurement time point.

**Time point**	**Instrument**	**Baseline (T0)**	**Immediately completing intervention (T1)**	**After 3 months (T2)**	**After 6 months (T3)**	**After 12 months (T4)**
Socioeconomic outcomes		√				
**Primary outcomes:**
Fear of cancer recurrence	FCRI	√	√	√	√	√
**Secondary outcomes:**
Salivary alpha amylase	Nipro salivary alpha amylase analyzer	√	√			
HRV	MP150-Biopac data acquisition system	√	√			
Attentional bias for FCR	The dot-probe task	√	√			
Rumination	CERQ-RS	√	√			
Catastrophizing	CERQ-CS	√	√			
Psychological symptoms	HADS	√	√	√	√	√
Self-compassion	SCS	√	√	√	√	√
Quality-adjusted life year	EQ-5D	√	√	√	√	√
Healthcare consumption	MCQ	√	√	√	√	√
Process outcomes			√			

#### Primary outcomes

Fear of cancer recurrence will be assessed using 42-item Fear of Cancer Recurrence Inventory (FCRI). This questionnaire consists of seven subscales, with a total score representing one's levels of FCR. A score of 13 or higher on 9-item severe subscale (ranges from 0 to 36) indicates a clinical FCR. The FCRI has been shown to have a good validity (convergent validity *r* = 0.68–0.77) and reliability (Cronbach's *alpha* = 0.95) (49).

#### Secondary outcomes

Neurophysiological data include *salivary alpha amylase* and *heart rate variability (HRV)*, and will take about 10 min to measure. The salivary alpha amylase activity will be measured by using a handheld salivary alpha amylase monitor manufactured by Nipro (Osaka, Japan). This analyzer can automatically measure the salivary alpha amylase activity within 1 min (about 30 s for saliva collection and 30 s for analyzing). Participants will be asked to brush teeth before measurement and not allowed to intake any food, beverage, tobacco or liquor within an hour. The HRV will be measured by using signal detection and amplification system (Biopac ECG100C) of MP150-Biopac data acquisition system. The Electrocardiogram (ECG) will be assessed with Lead-II configuration to measure participants' heart rate. The BiopacRSP100C will be used to collect respiratory rate, with filter rate ranges from 35 to 0.5 Hz. The CardioBatch will be used to analyze the ECG and respiratory rate, and compute the HRV. Participants will be asked not to intake any stimulant (e.g., caffeine and alcohol), or cannot do any strenuous activity within 4 h before measurement.

*Attentional bias for FCR* will be assessed by conducting the dot-probe task, including 200 trials with the stimuli of cancer-related words and utilized in previous study (52). The dot-probe task will be presented on a laptop computer and run by using Matlab. At the beginning of each trial, a “+” will present for 500 ms in the center of the screen. After that, a pair of word stimuli with a neutral word (e.g., apple) and a cancer-related word (e.g., chemotherapy) will be presented for 500 ms on the left and right sides of the screen. Then, the probe stimuli (i.e., “^*^” and “^**^”, representing the left and right button of the keyboard, respectively) will be presented in the position where the word stimuli just appear. Once the probe stimuli appear, participants should press button of the keyboard as soon as possible. After that, the screen will present 500 ms of blanking, and the next trial will start. Participants' reaction time to probe stimuli will be used to assess their attentional bias to cancer-related words. Cancer-related words are derived from a previous study examining attentional bias (52).

*Rumination* will be measured by using the 4-item Cognitive Emotion Regulation Questionnaire Rumination Subscale (CERQ-RS). Each item of CERQ-RS ranges from 1 to 5, and this subscale has been shown to have a good reliability with Cronbach's *alpha* of 0.83 (53).

*Catastrophizing thinking* will be measured by using the 4-item Cognitive Emotion Regulation Questionnaire Catastrophizing Subscale (CERQ-CS). Each item of CERQ-CS ranges from 1 to 5, and this subscale has been shown to have a good reliability with Cronbach's *alpha* of 0.79 (53).

*Psychological symptoms* will be measured by using Hospital Anxiety and Depression Scale (HADS). This 14-item questionnaire consisting of both anxiety subscale and depression subscale, rates on four-point (1–4) scales, and has been shown to have a good validity and reliability (54).

*Self-compassion* will be measured by using the 26-item Self-compassion Scale (SCS) consisting of six facets: self-kindness (5 items), self-judgment (5 items), common humanity (4 items), isolation (4 items), mindfulness (4 items), and over-identification (4 items) (55). Responses were rated on a five-point scale from 1 (*almost never*) to 5 (*almost always*). There is adequate evidence that SCS is valid and reliable (55).

The economic evaluation will be assessed with EuroQol-5D (EQ-5D). The EQ-5D includes five dimensions: mobility, self-care, usual activity, pain/discomfort, and anxiety/depression. Each dimension is assessed by one question with three levels of answers: no problem, some/moderate problems, and extreme problems. A health state can be obtained from a 5-digit number by combining the scores of each dimension. For instance, state 11,233 would indicate no problem with mobility or self-care, some problems with usual activities, and extreme problems with pain/discomfort, and anxiety/depression. The EQ-5D health states can be converted into an EQ-5D index to evaluate Quality-Adjusted Life Year (QALY). The EQ-5D has been widely used in cost-effectiveness analyses in various of clinical areas (56).

The *healthcare costs* of cancer patients in this study will be assessed with Medical Consumption Questionnaire (MCQ). It has been shown as a feasible and reliable instrument to measure medical consumption in patients with mental health problems (57).

#### Process outcomes

The process outcomes include participants' intervention adherence, satisfaction and acceptability. These outcomes will be assessed through self-report questionnaires completed by participants, and checklists and notes completed by researchers and therapists during the intervention.

### Cost-effectiveness analyses

The economic evaluation includes a cost-effectiveness analysis and a cost-utility analysis, both done from societal perspective. The cost-effectiveness analyses will calculate any incremental cost of each participant obtaining a significant decrease on FCRI Severity score (0.5 of the SD in FCRI Severity subscale is identified as a meaningful change) in both intervention and control groups (58). A lower incremental cost of each participant gaining a significant decrease on FCRI Severity score means higher cost-effectiveness of the group than another group. The cost-utility analysis will evaluate any incremental cost of each participant gaining a Quality-Adjusted Life Year (QALY) in therapy group. QALY will be calculated by using EQ-5D to measure Health-Related Quality of Life (HRQoL) weights (56).

The costs will be estimated from a societal perspective, and includes the costs related to therapy (excluding development or research costs), all healthcare costs and non-healthcare costs during the therapy. The therapy costs will be estimated based upon research team and hospital records (screening costs, delivery costs, and material costs of intervention). Other costs (i.e., healthcare costs and non-healthcare costs) will be estimated according to a resource use diary. The diary can be used to record patients' health service use (e.g., health consultations, hospitalization, emergency room visits, medication use, other psychological therapies use, and self-monitoring behaviors). The healthcare costs will be measured by Medical Consumption Questionnaire (MCQ) (57). Uncertainty in the cost and outcome will be estimated by non-parametric bootstrap analysis. The sensitivity analysis will be used to test the robustness of the economic evaluation results.

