### Aims of this study

In the current study, the Fear-focused Self-compassion Therapy, aiming to help Chinese young breast cancer patients to address FCR, has been developed. The primary aim of the current randomized controlled trial is to evaluate the effectiveness (i.e., both short-term and long-term effectiveness) and cost-effectiveness of Fear-focused Self-compassion Therapy in reducing severe FCR in young women with breast cancer, compared to usual care. Due to a lack of research comparing the cost-effectiveness between compassion-based therapy and usual care, it is hard to hypothesize which condition would be more cost-effective. This study expects that Fear-focused Self-compassion Therapy would be more cost-effective than usual care by reducing patients' FCR more effectively. Several specific hypotheses were outlined:

FCR severity would reduce to a larger extent in the Fear-focused Self-compassion Therapy condition (intervention group) compared to the treatment as usual condition (control group) from baseline and follow-up (3 months after treatment). The improvements in FCR can maintain at least 6 months after treatment.Symptoms of depression and anxiety would reduce to a larger extent in the Fear-focused Self-compassion Therapy condition compared to the treatment as usual condition from baseline and follow-up (3 months after treatment). These effects can maintain at least 6 months after treatment.Fear-focused Self-compassion Therapy would be cost-effective compared to treatment as usual.

The secondary aim of this study is to examine the underlying mechanisms of Fear-focused Self-compassion Therapy in reducing severe FCR. Specifically, the current research assumed that patients' improved dysfunctional cognitive evaluations and improved functioning of autonomic nervous system would play mediating roles between Fear-focused Self-compassion Therapy and improved FCR. Specific hypotheses are:

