### Sample size calculation

The sample size calculation is based on a previous psychological intervention research aimed at reducing breast cancer patients' FCR, with an effect size of *d* = 0.49 (46). The power analysis program G^*^Power was used to calculate the sample size. At least total 134 participants (67 participants in each group) need to be included to detect an effect of *d* = 0.49 with a power of 0.8 and two-side *alpha* level of 0.05. Considering the dropout of participants, we added 20% of the sample size. Therefore, this study needs a total of 160 participants, with 80 participants in each group.

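### The cost-effectiveness decision rule ranks the two arms on cost per responder, which an incremental ratio cannot do; applied as written it can favour the wrong arm, in either direction

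*Protocol article*

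**What the plan says.** The section Cost-effectiveness analyses defines a responder by a drop on the FCRI severity subscale, where "0.5 of the SD in FCRI Severity subscale is identified as a meaningful change". It then states what is calculated: "The cost-effectiveness analyses will calculate any incremental cost of each participant obtaining a significant decrease on FCRI Severity score", and this is to be done "in both intervention and control groups". The decision rule follows at once: "A lower incremental cost of each participant gaining a significant decrease on FCRI Severity score means higher cost-effectiveness of the group than another group".

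For QALYs the section says: "The cost-utility analysis will evaluate any incremental cost of each participant gaining a Quality-Adjusted Life Year (QALY) in therapy group". No rule for ranking groups is attached to that sentence.

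On uncertainty, "Uncertainty in the cost and outcome will be estimated by non-parametric bootstrap analysis", and a sensitivity analysis is also planned. Costs are taken from a societal perspective and cover therapy, healthcare and non-healthcare costs. Under Usual care, both arms have access to usual care.

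Aims of this study places cost-effectiveness within the primary aim and gives an expectation: "This study expects that Fear-focused Self-compassion Therapy would be more cost-effective than usual care by reducing patients' FCR more effectively". The Discussion repeats that aim. The Abstract lists cost-effectiveness among the secondary outcomes.

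**The concern.** The word incremental and the decision sentence do not fit together. An incremental ratio divides the difference in mean cost between the arms by the difference in effect between them, so there is one value per comparison. A rule that looks for the group with the lower value needs two values, one per arm. The only per-arm quantity available is the arm's mean cost divided by its responder proportion, which is an average ratio.

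Ranking average ratios does not show what the extra spending on therapy buys. An analyst who follows the sentence could report one arm as more cost-effective when the between-arm comparison, at the value a payer places on a responder, says the opposite. The hypothesis that therapy is cost-effective against usual care would then be settled by the wrong criterion.

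**Working it through.** **Inputs.** The documents give no cost, responder rate, ICER or willingness-to-pay value, so there is no figure of the plan's own to reproduce. Every cost below is an assumption in arbitrary units. Write C1 and C0 for mean cost per participant and p1 and p0 for responder proportion (1 = therapy, 0 = usual care).

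**Quantities.**
- Rule as written: prefer therapy if C1/p1 < C0/p0.
- ICER = (C1 − C0)/(p1 − p0), judged against a willingness to pay per additional responder, λ.
- Incremental net benefit = λ(p1 − p0) − (C1 − C0); prefer therapy if it is positive.

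**What the rule amounts to when p1 > p0.**
1. C1/p1 < C0/p0 is the same as C1·p0 < C0·p1.
2. Subtract C0·p0 from both sides: (C1 − C0)·p0 < C0·(p1 − p0).
3. Divide by p0(p1 − p0), which is positive: ICER < C0/p0.

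So the rule compares the ICER with usual care's average cost per responder. That figure plays the part of λ, but it reflects background spending in the control arm and not what an additional responder is worth.

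**Example 1 (assumed responder rates 55% and 30%, cost difference 1,500).**

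| | Therapy cost | Usual care cost | C1/p1 | C0/p0 | Rule picks | ICER |
|---|---|---|---|---|---|---|
| Base | 2,500 | 1,000 | 2,500/0.55 = 4,545 | 1,000/0.30 = 3,333 | usual care | 1,500/0.25 = 6,000 |
| 5,000 added to each arm | 7,500 | 6,000 | 7,500/0.55 = 13,636 | 6,000/0.30 = 20,000 | therapy | 1,500/0.25 = 6,000 |

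Therapy buys the same extra responders for the same extra money in both rows, yet the rule reverses. The switch comes when C0/p0 passes the ICER: (1,000 + x)/0.30 = 6,000 gives x = 800.

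Incremental net benefit is the same in both rows:
- At λ = 10,000: 0.25 × 10,000 − 1,500 = +1,000. Therapy is preferred, so the rule is wrong in the base row.
- At λ = 5,000: 0.25 × 5,000 − 1,500 = −250. Usual care is preferred, so the rule is wrong in the second row.

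**Example 2 (responder rates tied to the planned effect).** Sample size calculation plans "with an effect size of *d* = 0.49", and the responder cut-off is 0.5 SD. Assume normal changes, an SD of change equal to the baseline SD, and no mean change under usual care. Then p0 = 1 − Φ(0.50) = 0.309 and p1 = 1 − Φ(0.50 − 0.49) = 0.496.
- Costs 4,000 and 2,000: arm ratios 8,064 (therapy) and 6,482 (usual care), so the rule picks usual care. The ICER is 10,668, so therapy is preferred at any λ above that.
- Costs 15,000 and 10,000: arm ratios 30,241 (therapy) and 32,411 (usual care), so the rule picks therapy. The ICER is 26,670, so usual care is preferred at any λ below that.

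Varying the SD of change from 0.7 to 1.3 baseline SD and the mean usual-care improvement from 0 to 0.2 SD gives p0 from 0.24 to 0.41 and p1 from 0.49 to 0.61. The algebra does not depend on these values.

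**The case against.** The best defence is that an ICER was intended. The section uses the word incremental throughout, never mentions an average ratio, and the hypotheses compare therapy with usual care. The phrase about both groups might mean only that responders are counted in both. This is a fair reading of intent, and it makes the fault an internal contradiction and not a clear choice of average ratios. It does not rescue the decision sentence, because no reading lets a single between-arm ratio be lower in one group than in the other.

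The rule is also not always wrong. It agrees with the ICER when therapy is both cheaper and more effective, or when willingness to pay lies on the same side of the ICER as C0/p0. That is true, but nothing in the plan ensures it. The bootstrap and sensitivity analyses describe uncertainty and do not change which quantity decides.

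It is fair too that willingness-to-pay ranges and acceptability curves are commonly left to a full analysis plan. Their absence from the article is no fault; the fault is the rule that the article does state.

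A reader might infer that the rule is biased against therapy, because patients selected for high FCRI severity will partly improve without it. The documents do not support this. Regression to the mean acts in both arms, and the direction depends on background costs, which are not given. A reader might also infer that the cost-utility ratio is computed in the therapy arm alone. That sentence carries no ranking rule and can be read as the ordinary extra cost per QALY gained with therapy.

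**Conclusion.** The point stands for one decision sentence, which contradicts the incremental quantity it is meant to judge. If therapy is the more effective arm, the sentence applied literally favours therapy exactly when the ICER is below usual care's average cost per responder. Costs shared by both arms can therefore settle the conclusion: in Example 1, anything above 800 added to each arm reverses it. The algebra is exact. How large or likely an error would be in this trial cannot be judged, because all costs and responder rates here are assumed.

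The consequence is confined to the economic conclusion. That conclusion matters because cost-effectiveness is within the primary aim, although the Abstract ranks it as secondary. The comparison of FCRI severity under Statistical analyses, the sample size and the data collection are unaffected.

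**What to change.** Delete the sentence that ranks the groups. In its place define one between-arm ratio:

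ICER = (mean cost therapy − mean cost usual care)/(responder proportion therapy − responder proportion usual care).

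State that it is judged against willingness to pay, for example by incremental net benefit or by an acceptability curve from the bootstrap already planned. For clarity, word the cost-utility sentence as the same between-arm ratio with mean QALYs in the denominator.

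The cost is a few lines of text and matching analysis code. Costs, FCRI and EQ-5D are already planned in both arms, so no new data and no change to conduct are needed. The change should be made before results are seen.
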